## BIOSCIENCE INSTRUCTIONS AND TEMPLATE

NUMBER

DATE

PAGE

HRP-503b

3/22/2022

1 of 13

### Instructions and Notes:

- Depending on the nature of what you are doing, some sections may not be applicable to your research. If so mark as "NA".
- When you write a protocol, keep an electronic copy. You will need to modify this copy when making changes.

### 1 Protocol Title

Diabetes Prevention for Latino Youth with Prediabetes

### 2 Background and Objectives

Provide the scientific or scholarly background for, rationale for, and significance of the research based on the existing literature and how will it add to existing knowledge.

- Describe the purpose, specific aims, or objectives.
- State the hypotheses to be tested.
- Describe the relevant prior experience and gaps in current knowledge.
- Describe any relevant preliminary data.

## BIOSCIENCE INSTRUCTIONS AND TEMPLATE

NUMBER

HRP-503b

DATE

3/22/2022

PAGE

2 of 13

Type 2 Diabetes (T2D) is a major public health burden that reduces quality of life (QoL) and longevity. Disparities in T2D emerge early in life and disproportionately impact obese Latino youth. The CDC estimates that up to 50% of Latino children will develop T2D in their lifetime. Given that youth onset T2D is estimated to reduce life expectancy by 15 years, a public health imperative is to prevent this chronic disease in youth. The Diabetes Prevention Program (DPP) established that T2D is preventable through lifestyle intervention in adults with prediabetes, yet to date, no T2D prevention studies for prediabetic Latino youth exist in the literature.

Intensive and targeted T2D prevention efforts for youth who are already obese and exhibit prediabetes are critical, as this group is at imminent risk for conversion to T2D and the associated complications. In prediabetic adults, weight loss is the primary factor mediating T2D prevention. In contrast we have shown, through a series of lifestyle interventions in obese Latino youth, that significant health improvements occur independent of weight loss. Since obese youth are still developing, improvements in body composition may be more physiologically relevant for T2D prevention. Therefore, we propose that weight loss may not be the optimal target for preventing T2D in obese prediabetic youth. This paradigm acknowledges that 1) most obese adolescents will remain obese for the rest of their lives, 2) improving metabolic health in obese adolescents is not necessarily linked to weight loss, and 3) intermediate T2D outcomes (e.g., glucose tolerance and insulin sensitivity) are needed to appreciate T2D risk reduction in response to intervention. In addition, reframing intervention goals and outcomes around improved health and well-being rather than weight loss per se will further enhance program compliance, retention, and ultimately success among obese youth.

Challenges to implementing effective diabetes prevention programs for Latino youth with prediabetes include disparities in access to care, cultural norms surrounding obesity and diabetes, and poor health literacy in low income, Spanish-speaking families. Unfortunately, the current healthcare system is poorly equipped to address these contextual factors and meet diabetes prevention needs of obese Latino youth with prediabetes.

Our transdisciplinary team of researchers, practitioners, and community partners has collaborated for the past 7-years to effectively address diabetes prevention challenges through the development, testing, refinement, and expansion of a culturally-grounded lifestyle intervention for obese Latino youth with prediabetes, which if efficacious, could be taken to scale. The overall approach applies an adapted Ecodevelopmental framework to leverage community, family, peer, and individual-level influences during the critical transition period of adolescence when changes in health behaviors and health outcomes are linked to future health trajectories. The intervention draws upon Social Cognitive Theory and employs key behavioral modification strategies from the DPP to enhance self-efficacy and foster social support for making healthy behavior changes. *Promotores* (community health workers) deliver nutrition education to families to facilitate dietary changes while group exercise classes for youth are led by YMCA staff to increase physical activity levels. Feasibility and initial efficacy for improving glucose tolerance and increasing insulin sensitivity was established through a pilot study. The pilot intervention also led to significant improvements in QoL, eating behaviors, fitness, and multiple cardiovascular disease risk factors without weight loss. We are currently conducting an RCT that expands upon the pilot to rigorously evaluate intervention effects in obese Latino adolescents. To date, we have enrolled 160 obese youth and the rate of prediabetes in this community sample is ~15%. Preliminary analyses on prediabetic youth show robust and sustained improvements on targeted outcomes including glucose tolerance, insulin sensitivity, and QoL. For ethical reasons, we do not randomize prediabetic youth to the control condition in that study. We now propose to build upon these compelling preliminary findings and further refine our culturally-grounded lifestyle intervention to test the efficacy, as compared to usual care, for improving health and QoL by **preventing T2D in obese Latino adolescents with prediabetes**.

**Specific Aim 1:** Test the short-term (6-month) and long-term (12-month) efficacy of this culturally-grounded, community-based lifestyle intervention as compared with a usual care control group for improving glucose tolerance and increasing insulin sensitivity in 120 obese Latino adolescents age 12-16 with prediabetes.

**Specific Aim 2:** Compare intervention effects to usual care on changes in QoL.

**Specific Aim 3:** Explore the mediating effects of changes in body composition on changes in T2D risk markers.

**Specific Aim 4:** Estimate the incremental cost effectiveness for improving glucose tolerance between groups.

## BIOSCIENCE INSTRUCTIONS AND TEMPLATE

NUMBER

HRP-503b

DATE

3/22/2022

PAGE

3 of 13

### 3 Data Use

Describe how the data will be used. Examples include:

- Dissertation, Thesis, Undergraduate honors project
- Publication/journal article, conferences/presentations
- Results released to agency or organization
- Results released to participants/parents
- Results released to employer or school
- Other (describe)

- **Data will be used in dissertation, thesis, and undergraduate honors projects.**
- **Data will be used for publication/journal article, conferences/presentations.**
- **Results may be released to agencies or organizations.**
- **Results may be released to participants.**

### 4 Inclusion and Exclusion Criteria

Describe the inclusion and the exclusion criteria for the study.

Describe how individuals will be screened for eligibility.

Indicate specifically whether you will target or exclude each of the following special populations:

- Minors (individuals who are under the age of 18)
- Adults who are unable to consent
- Pregnant women
- Prisoners
- Native Americans
- Undocumented individuals

#### Inclusion Criteria:

- Latino: self-report
- Age: 12-16
- Obese: BMI percentile  $\geq 95$ th percentile for age and gender or BMI  $\geq 30$  kg/m^2
- Prediabetic: fasting glucose  $\geq 100$  and/or 2-hour post-OGTT glucose  $\geq 120$  mg/dl

#### Exclusion Criteria:

- Taking medication(s) or diagnosed with a condition that influences carbohydrate metabolism, PA, and/or cognition
- Type 2 diabetes: Fasting glucose  $\geq 126$  mg/dl or 2-hour glucose  $\geq 200$  mg/dl.
  - Youth found to be diabetic upon screening will be referred for follow-up care
- Recent Hospitalization (previous 2 months)
- Currently enrolled in (or within previous 6 months) a formal weight loss program.
- Diagnosed depression or other condition that may impact QoL
- Pregnant

### 5 Number of Participants

Indicate the total number of participants to be recruited and enrolled

- Provide a rationale for the proposed enrollment number
- What percentage of screened individuals will likely qualify for the study?

**We will screen ~300 obese Latino youth for prediabetes and anticipate that 120 will meet eligibility into the trial. These estimates are based on rates of elevated 2-hour glucose in our current study (~40% exhibit 2-hour glucose  $\geq 120$  mg/dl).**

### 6 Recruitment Methods

- Describe when, where, and how potential participants will be identified and recruited.
- Describe materials that will be used to recruit participants. (Attach copies of these documents with the application.)
- Does any member have a dual role with the study population?

## BIOSCIENCE INSTRUCTIONS AND TEMPLATE

NUMBER

HRP-503b

DATE

3/22/2022

PAGE

4 of 13

Recruitment will be coordinated by our clinical partner from the Family Diabetes Program at the St. Vincent de Paul Medical and Dental Clinic, an established and trusted entity in the local Latino community. The clinic provides primary and specialty services to Latino children and families and pulls from a referral network of over 100 schools, community centers, and healthcare organizations in the greater Phoenix area. This referral network is our primary source of recruitment for our ongoing RCT in a similar population where we have successfully met our recruitment schedule. Successful recruitment efforts are facilitated through distribution of flyers, hosting presentations, attending health fairs, and direct contact/referral by providers (see letters of support). Additional aspects that facilitate successful recruitment and enrollment include, 1) bilingual / bicultural research staff to assist with recruiting, consenting, enrollment and data collection, 2) pediatric and specially trained research nursing staff in our clinical unit, 3) assistance with transportation to and from research and intervention facilities, 4) appropriate compensation for time and effort, 5) A Community Advisory Board of trusted community organizations serving Latino families (see letter of support from CAB Chair), 6) providing families the results of the metabolic testing, and most importantly 7) providing an intervention with a high likelihood of directly benefiting individuals enrolled.

### 7 Study Timelines

Describe:

- The duration of an individual participant's participation in the study.
- The duration anticipated to enroll all study participants.
- The estimated date for the investigators to complete this study (up to and including primary analyses).

Each participant will be enrolled for ~13 months and we anticipate that it will take ~3.5 years to enroll the entire sample. We anticipate that the study will be completed in November of 2021.

## BIOSCIENCE INSTRUCTIONS AND TEMPLATE

NUMBER

HRP-503b

DATE

3/22/2022

PAGE

5 of 13

### 8 Procedures Involved

Describe and explain the study design. Provide a description of all research procedures being performed and when they are performed.

Describe procedures including:

- The documents/ measures / devices/ records /sampling that will be used to collect data about participants. (Attach all surveys, scripts, and data collection forms.)
- What data will be collected including long-term follow-up?
- All drugs and medical devices used in the research and the purpose of their use, and their regulatory approval status.
- Describe the available compensation (monetary or credit that will be provided to research participants).
- Describe any costs that participants may be responsible for because of participation in the research.

**Design:** This is a randomized controlled intervention to test the short-term (6-months) and long-term (12-months) efficacy of a culturally-grounded lifestyle intervention to improve glucose tolerance in obese Latino adolescents with prediabetes compared to a UCC group. We will further determine effects on QoL, explore the mediating effects of changes in total body fat on T2D risk reduction, and examine the initial incremental cost effectiveness of the intervention to improve glucose tolerance compared to usual care control.

**Informed consent:** Written informed consent and assent will be obtained from the parent/guardian and adolescent prior to any procedures. Participants will be informed they are free to withdraw from the study at anytime, that nonparticipation will not affect services, and that confidentiality will be maintained. All study-related documents will be approved by the ASU IRB and materials will be available in English and Spanish with bilingual/bicultural research staff administering consent, collecting data, and answering questions.

**Health Screening and Metabolic Phenotyping:** Potential participants will arrive at the ASU Clinical Research Unit at ~8:00 AM after an overnight fast for initial screening including a brief health history, height and weight measurement to calculate BMI percentile, and a standard 75g OGTT for fasting and 2-hour glucose (assessed by SonoraQuest Laboratories). Participants meeting inclusion criteria (described above) will return within 4 weeks of the screening OGTT for baseline testing to include in-depth medical and family history (including in utero exposure to gestational diabetes) and a brief physical exam. Height, weight, and waist circumference will be measured to the nearest 0.1cm, 0.1 kg, 0.1cm, respectively. Sitting blood pressure will be measured in triplicate using an appropriately-sized cuff on the right arm after 5 min of rest. A fasting lipid panel will be collected to measure cholesterol (Total, HDL, and LDL), triglycerides, and HbA1c. These assessments follow current recommendations for screening in obese youth, will be used in the curriculum to discuss the health risks of obesity, and are an important and meaningful benefit to families.

**Glucose Tolerance and Insulin Sensitivity (Aim 1):** Glucose tolerance and insulin sensitivity will be assessed by a 75 gram OGTT with multiple blood sampling for insulin glucose. Blood samples will be collected from an in-dwelling catheter at -15', -5', 30', 60', 90' and 120' for measurement of plasma glucose (glucose oxidase, YSI INC., Yellow Springs, OH) and insulin (ELISA, ALPCO Diagnostics, Windham, NH). At time 0', participants will ingest 75 grams of glucose in solution. Improvements in glucose tolerance will be assessed by decreases in 2-hour glucose levels (primary outcome) while changes in insulin sensitivity will be estimated by the whole-body insulin sensitivity index. For the purposes of this study, glycemic status will be defined as "Normal" (fasting glucose <100 mg/dl and 2-hr glucose <120 mg/dl), "Prediabetic" (fasting glucose ≥100 mg/dl or 2-hr glucose ≥120 mg/dl), or "Diabetic" (fasting glucose ≥126 mg/dl or 2-hr glucose ≥200 mg/dl). **NOTE:** Youth identified as "diabetic" at any point in the study will be referred for follow-up care and given the option to continue with the study with clearance from their physician.

**Quality of Life (Aim 2):** QoL will be assessed using the Youth Quality of Life (YQOL) inventory. The YQOL was developed through semi-structured interviews with youth regarding positive and negative aspects of QoL. Domains of self (feelings about one's self), social relationships (friends and family), environment (social and cultural milieu) are assessed and an overall QoL score is computed. Weight-specific QoL will be assessed by the YQOL-W which, measures three domains of weight-related QoL (Self, Social, and Environmental). It is specific to obese adolescents (11-18 years) for use in evaluating weight management interventions in clinical and community research. Both instruments will be self-administered prior to any anthropometric procedures and can be completed in <15 minutes.

**Total Body Composition (Aim 3):** Total body composition (fat, muscle, and bone) will be assessed by Dual-energy X-Ray Absorptiometry (DXA) using the GE Lunar iDXA (GE Lunar, Madison, WI). DXA provides reasonable estimates of total body composition as well as changes in fat mass and lean tissue mass following lifestyle intervention in obese youth. Total scan time will be ~ 15 minutes while the DXA arm passes over the entire body. DXA scans will be performed upon completion of the OGTT, prior to eating. A urine pregnancy test will be performed in females in the ASU Clinical Research Unit with a negative test required before each DXA measurement (baseline, 6- and 12-months). Pregnant females will be excluded.

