## BIOSCIENCE INSTRUCTIONS AND TEMPLATE

NUMBER

HRP-503b

DATE

3/22/2022

PAGE

11 of 13

**Specific Aim 1:** We will test the hypothesis that adolescents who complete the intervention will exhibit significantly greater short-term and long-term improvements in glucose tolerance and increases in insulin sensitivity compared to UCC. ANCOVA models will use pretest measures as a covariate and the experimental groups (i.e., intervention vs. UCC) for comparisons. Separate analyses will be conducted for 6- and 12-months. We will explore interactions between the covariate (baseline measure) and group to determine whether adolescents with lower baseline scores differentially benefit from the program. Assuming no interaction is found, we will examine the main effect of group assignment on the outcome measure after adjusting for baseline. We will also conduct repeated measures ANCOVA models to examine differences in the effect of the intervention on primary outcomes between 6- and 12-month time points.

**Specific Aim 2:** We will use the same ANCOVA models described above to examine the effects of the intervention on general and weight-specific QoL. Results will indicate whether adolescents who were randomized to the intervention report greater increases in QoL compared to adolescents randomized to UCC.

**Specific Aim 3:** We will explore the mediating effects of changes in total body composition on changes in T2D risk markers by path analysis. Each mediation model will include three variables: (1) experimental group membership represented by dummy codes, (2) a mediator measure (e.g., fat mass), and (3) an outcome measure. The model specifies direct paths from group membership to the mediator and outcome. Path coefficients and standard errors for these paths will be estimated. Effect size measures will include: (1) direct effects on outcome and (2) mediated or indirect effects on outcome. The latter will be estimated using path coefficient estimates with standard errors.

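### The primary outcome, 2-hour glucose, has no primary time point: it is tested separately at 6 and 12 months, with no rule on which result decides

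*Supplement*

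**What the plan says.** Section 8 (Glucose Tolerance and Insulin Sensitivity) gives the primary label to 2-hour glucose alone: "Improvements in glucose tolerance will be assessed by decreases in 2-hour glucose levels (primary outcome". The same sentence goes on to insulin sensitivity without that label: "while changes in insulin sensitivity will be estimated by the whole-body insulin sensitivity index". No visit is attached to either measure.

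The two visits appear side by side wherever efficacy is described. Specific Aim 1 in section 2 reads "Test the short-term (6-month) and long-term (12-month) efficacy of this culturally-grounded, community-based lifestyle intervention", and covers "improving glucose tolerance and increasing insulin sensitivity in 120 obese Latino adolescents". The Design paragraph of section 8 calls the study a "randomized controlled intervention to test the short-term (6-months) and long-term (12-months) efficacy". Neither place ranks one visit above the other.

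Section 16 (Specific Aim 1) sets out ANCOVA adjusted for the baseline value and states: "Separate analyses will be conducted for 6- and 12-months". It then adds "repeated measures ANCOVA models to examine differences in the effect of the intervention on primary outcomes between 6- and 12-month time points". The plural is not explained, and the outcomes it covers are not listed.

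A single time point is chosen in only one place. Section 16, Specific Aim 4, uses 2-hour glucose at 12 months for the cost-effectiveness base case, and that choice does not extend to Aim 1.

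**The concern.** A primary outcome fixes in advance which result decides the trial. Here the variable is fixed but the visit is not, and each visit has its own analysis. If the two disagree, the sponsor can present the favourable one as the primary result without departing from the protocol.

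Disagreement is easy to foresee. The intensive phase ends at 6 months and is followed by only three booster sessions, in months 7, 8 and 9, so a gain at 6 months could fade by 12. The protocol does not say whether the trial would then have met its primary outcome.

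The shift from singular in section 8 to plural in section 16 adds a second doubt: whether the plural means 2-hour glucose at two visits, or 2-hour glucose together with insulin sensitivity.

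**Working it through.** **The plan's own figure.** The only sample-size arithmetic is in section 5: 300 screened × 0.40 eligible = 120. This reproduces, but it is a recruitment yield. It implies no significance level, so it cannot settle the error rate.

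**Inputs from the documents.** One variable labelled primary (section 8). Two time points, each with its own ANCOVA (section 16). No ranking and no success rule.

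**Assumptions, not in the documents.** (a) Each test is two-sided at 5%. (b) Either significant result counts as success. (c) The correlation ρ between the 6- and 12-month test statistics lies between 0 and 0.8.

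**Two tests of 2-hour glucose, no true effect.**

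- Independent tests, either direction: 1 − 0.95² = 9.75%.
- Independent tests, in the intervention's favour only: 1 − 0.975² = 4.94%, against 2.5% for a single test.
- Correlated tests: 1 − P(|Z₁| ≤ 1.96 and |Z₂| ≤ 1.96), from 2,000,000 simulated pairs of correlated normal statistics. The last column counts only Z > 1.96.

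| ρ between visits | Either direction | Favouring the intervention |
|---|---|---|
| 0 | 9.75% | 4.94% |
| 0.3 | 9.5% | 4.8% |
| 0.5 | 9.05% | 4.5% |
| 0.7 | 8.3% | 4.2% |
| 0.8 | 7.8% | 3.9% |

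This gives about 8-10% two-sided, of which about 4-5% favours the intervention. At ρ = 0.9 the figures would fall to 7.0% and 3.5%.

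**Four tests, only if insulin sensitivity is also read as primary.** Independent: 1 − 0.95⁴ = 18.5%. With correlation between visits and between measures (the cross-correlation taken as their product):

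| ρ visits | ρ measures | Either direction | Favouring the intervention |
|---|---|---|---|
| 0.5 | 0.5 | 16.1% | 8.1% |
| 0.7 | 0.7 | 13.7% | 6.9% |
| 0.8 | 0.7 | 12.8% | 6.4% |

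**The opposite rule.** If every test had to be significant, the error rate could not exceed that of a single test, 5%.

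**After the fix.** The second time point is tested only if the first is significant. With no effect at either visit, a false claim therefore requires a false positive on the first test: 5.0% two-sided, 2.5% in the intervention's favour.

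**The case against.** A reader might infer that the plan grants four full-strength chances to declare efficacy, with a false-positive rate of up to 19%. The documents do not support that:

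- Section 8 labels only 2-hour glucose as primary, and the Design paragraph speaks of glucose tolerance alone. A second primary variable rests on one plural in section 16. That plural stands in a sentence comparing visits, so it may mean one variable at two times.
- The 19% end needs four independent tests. These would be repeated measures on the same adolescents, with both indices from the same glucose tolerance test.
- About half of these errors favour usual care and would not be read as efficacy.

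Three further objections carry weight. First, the Aim 1 hypothesis joins its parts with *and*. Read literally, all must succeed and there is no inflation. Alternatively, short-term and long-term efficacy may be two questions, each with its own claim. Both readings are possible and the text chooses neither. That ambiguity is the fault, and it means the inflated rate is conditional.

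Second, a split result would not be uninterpretable. The repeated-measures ANCOVA is meant to compare the effect at the two visits, so a fading gain could be described as short-term without long-term efficacy. That analysis still does not say which visit decides the primary outcome.

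Third, no separate analysis plan is shown, and the significance level and multiplicity method are commonly left to one. Their absence is not held against the protocol. The visit at which the primary outcome is judged is core protocol content, and the singular-plural conflict lies within the protocol itself.

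**Conclusion.** The point holds for 2-hour glucose at two visits. The protocol has one labelled primary variable, two unranked time points, a separate test at each, and an unexplained change from singular to plural. The 12-month choice under Aim 4 does not resolve this.

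The 8-10% rate, with its 4-5% share in the intervention's favour, is conditional on assumptions (a) to (c). It is the cost of one permissible reading and not a property the plan declares. The four-test figures, about 13-16% at correlations of 0.5 to 0.8, apply only if insulin sensitivity was meant to be primary too, which section 8 does not say.

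This should be corrected. It does not call the design, the randomised comparison or the ANCOVA model into question.

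**What to change.** In sections 8 and 16:

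1. Name 2-hour glucose at one time point as the single primary endpoint. The choice between 6 and 12 months is the sponsor's and should be recorded before analysis.
2. Test 2-hour glucose at the other time point at two-sided 5%, and only if the first test succeeds.
3. Call insulin sensitivity secondary in both sections, and replace the plural in section 16 with the named endpoint.

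The cost is wording. No further participants are needed and the first test keeps its full 5%. The downside is that the second time point cannot be claimed as confirmatory if the first fails, so the order should follow the question the sponsor most needs answered.
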